### **Second visit**

Fear will be measured followed by random allocation into test and control sub-groups and implementation of the intervention.

This visit will start by application of Facial Image Scale (FIS) with every child in each group. It is a visual analog scale comprising of a row of five faces ranging from very happy to very unhappy. Children will be asked to point at which face they feel most like at the moment. The face will be scored by giving a value of one to the most positive affect face and five to the most negative affect face with faces 4 and 5 indicating high dental fear (Appendix III). 

After that, all procedures will be explained to the child using the *Tell Show Do* (TSD) Technique.  Standardized words as well as procedures and environment will be used for each child during intervention in the dental clinic. Children in the control sub-group will be accompanied by their parent who will sit in passively in the dental operatory behind the patient with no eye contact. Children in test sub-group will be accompanied by their parent who will stand in close proximity to their child with hand holding and may help in explaining the dentist's instructions. 

Non-pain provoking dental treatment will follow including: oral prophylaxis, fissure sealant  and topical fluoride applications. 

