It is evident that a strong relationship exists between dental fear and children's behavior.  However, limited research has dealt with the effect of children's intelligence on their fear and consequently on their behavior in the dental clinic.  In addition, no research has investigated active versus passive presence of parents in the dental operatory and its effect on the child's behavior. These problems have furnished the stimulus for the present investigation.

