### **Study Sample**

#### ***Sample size estimation***

Sample size was based on assuming 5% alpha error, 20% beta error, allocation ratio between test and control subgroups of 1:1, and probability of positive behavior in the control subgroup of low intelligence quotient (IQ) = 0.25.  An estimation was made of the probability of positive behavior in the test subgroup with low IQ to have positive behavior as healthy children = 0.87.  So, to detect the difference between control and test groups, it was calculated that 9 children per subgroup would be needed.  To ensure adequate power, we estimated a reduction in the difference between test and control groups regarding probabilities of positive behavior of 50% with calculated required number= 24. This was increased to 25 children per subgroup to account for non-completion. Thus, the total required number of children= number of groups X number of subgroups X number per group= 3 X 2 X 25= 150 children.

Visual Screening and parent meeting will be carried out to identify children who will fulfill the inclusion criteria.

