### **Randomization and allocation concealment**

Children will be stratified based on their IQ into 3 groups: high, average, and low IQ groups. In each group, children will be randomly and equally allocated according to intervention into test and control sub-groups. The study will thus include

6 subgroups. Randomization will be performed by a trial independent person using computer random number generator. Randomization sequence in blocks of 2 will be created using random allocation software version 1.0.0. The allocated group will be written on piece of paper which will be folded and enclosed in a sealed envelope carrying the child's name on its cover. At the time of intervention, an assistant will open the envelope, identify the sub-group to which the child will be assigned.

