### **Statistical Analysis**

Descriptive statistics will be calculated as frequencies and percent. The comparison between test and control sub-groups will be done using Chi-squared test. Logistic regression analysis will be conducted to assess the effect of the groups (based on IQ level), subgroups (test or control) and confounders (fear, gender, and age) on the outcome (behavior dichotomies into positive and negative behaviors). Statistical analysis will be done using SPSS version 17.0 (SPSS Inc., Chicago, Ill., USA). Significance level will be set at 5 %.

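### The within-IQ-group comparison of test and control uses a raw chi-squared test that leaves out baseline fear, which the protocol scores before allocation and already names as a confounder

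*Protocol*

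**What the plan says.** - **Timing.** Protocol, Second visit: "Fear will be measured followed by random allocation into test and control sub-groups and implementation of the intervention". The Facial Image Scale (FIS) score is known before the arm is.
- **Importance of fear.** Introduction: "It is evident that a strong relationship exists between dental fear and children's behavior". The title, aim and PICO question also place fear beside intelligence.
- **Allocation.** Randomization and allocation concealment: "Children will be stratified based on their IQ into 3 groups: high, average, and low IQ groups", then "In each group, children will be randomly and equally allocated according to intervention into test and control sub-groups". Fear is not a stratification factor. The sub-groups defined here lie inside IQ groups.
- **Size.** Sample size estimation plans 25 children in each of six sub-groups, 150 in all, and argues from test and control rates in low-IQ children.
- **Analysis.** Statistical Analysis: "The comparison between test and control sub-groups will be done using Chi-squared test". The same section plans a logistic regression on IQ group, "subgroups (test or control) and confounders (fear, gender, and age) on the outcome". It lists no IQ-by-arm term.
- **Fear levels.** Outcome assessment defines faces 1-2 as low, 3 as moderate and 4-5 as high fear.

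**The concern.** The comparison that the sample size section sizes is test versus control inside one IQ group. As written, it takes no account of a baseline score that the protocol holds to be closely tied to the outcome. The logistic model does use fear but, on the terms listed, it gives one arm effect common to all IQ groups. The IQ-specific results are therefore the ones left without fear adjustment.

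Two things are at stake. If fear does predict behaviour, variation that could be removed stays in the IQ-specific estimate. And with 25 children per arm, a visible chance difference in fear in one IQ group could be taken for an IQ-specific benefit or harm, with no planned analysis to answer it.

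**Working it through.** **Inputs from the protocol.** 25 per sub-group; control rate 0.25; test rate 0.87; difference halved from 0.62 to 0.31, giving 0.25 versus 0.56; alpha 5%; beta 20%. **Assumed, not in the protocol:** share of children with high fear (10-40%) and the odds ratio by which high fear lowers positive behaviour (1 to 10).

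**1. The plan's own figure.** With n = [1.96·√(2p̄(1−p̄)) + 0.8416·√(p₁(1−p₁)+p₂(1−p₂))]² / d²:
- 0.25 versus 0.87: (1.376 + 0.461)² / 0.3844 = 8.8, so 9. This matches the protocol.
- 0.25 versus 0.56: (1.361 + 0.554)² / 0.0961 = 38.2, so 39, not the stated 24. That is a separate matter. It is noted here because it explains why the baseline power below is about 0.65 rather than 0.80.

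**2. Chance imbalance in fear.** Let X and Y be the numbers of high-fear children in two arms of 25, each binomial(25, q). The SD of the gap is √(2q(1−q)/25). A gap of 20 points or more means |X−Y| ≥ 5.

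| High-fear share q | SD of gap | P(gap ≥ 20 points), one IQ group | At least one of three, 1−(1−P)³ |
|---|---|---|---|
| 10% | 8.5 points | 3.4% | 9.7% |
| 20% | 11.3 points | 11.0% | 29.4% |
| 30% | 13.0 points | 16.4% | 41.5% |
| 40% | 13.9 points | 19.3% | 47.5% |

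**3. What such a gap does.** Take q = 30% and odds ratio 6. An overall control rate of 0.25 splits into 0.325 (not high fear) and 0.074 (high fear): 0.7×0.325 + 0.3×0.074 = 0.25. A test rate of 0.56 splits into 0.686 and 0.267. A 20-point gap moves the raw risk difference by 0.20×(0.325−0.074) = 0.050 if it sits in the control arm and by 0.20×(0.686−0.267) = 0.084 if it sits in the test arm. That is 16-27% of the planned 0.31.

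**4. Precision of the IQ-specific risk difference.** Raw: √[(0.25×0.75 + 0.56×0.44)/25] = 0.132. With fear perfectly balanced and adjusted for, at q = 30% and odds ratio 6, the variance contributions are 0.7×0.325×0.675 + 0.3×0.074×0.926 = 0.174 (control) and 0.7×0.686×0.314 + 0.3×0.267×0.733 = 0.210 (test), so √(0.384/25) = 0.124. Simulation (60,000 IQ groups per setting, 25:25 allocation ignoring fear) gives the Mantel-Haenszel risk difference and test without any change to the lists:

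| Fear share, odds ratio | SD, raw | SD, Mantel-Haenszel | Change | Power, raw | Power, Mantel-Haenszel |
|---|---|---|---|---|---|
| 20-40%, 1 (no effect) | 0.132 | 0.133 | +1% | 0.65 | 0.61 |
| 20%, 3 | 0.132 | 0.131 | −1% | 0.65 | 0.63 |
| 40%, 3 | 0.132 | 0.129 | −2% | 0.65 | 0.64 |
| 30%, 6 | 0.132 | 0.126 | −4% | 0.65 | 0.66 |
| 20%, 10 | 0.132 | 0.127 | −4% | 0.65 | 0.66 |
| 40%, 10 | 0.132 | 0.120 | −9% | 0.65 | 0.71 |

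Adding fear-stratified lists at 30% and odds ratio 6 takes the SD from 0.126 only to 0.124.

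**5. Type I error.** The exact size of the uncorrected chi-squared test at 25 versus 25 and 0.40 versus 0.40, with no fear effect at all, is 0.060. Simulated with fear effects it stays at about 0.06. Mantel-Haenszel runs at about 0.05. The excess comes from the discreteness of the uncorrected test and has nothing to do with fear.

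**The case against.** Four points deserve a fair hearing.

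**Fear is not ignored.** The Statistical Analysis section names it as a confounder in the logistic model. A reader might infer that the arm analysis as a whole omits fear; it does not. Whether an IQ-by-arm term is fitted could also be settled in a statistical analysis plan that is not shown. The point is therefore confined to the sub-group comparison, for which the protocol does name the test.

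**The within-IQ reading is an inference.** The section never says that the chi-squared test is run separately by IQ group. The way the randomisation and sample size sections build the sub-groups makes that the natural reading, not a certain one. If the test pools 75 versus 75, a fear gap of 20 points or more (at least 15 children) has a chance of only 0.3-1.5% at 20-40% high fear, and little of the point remains.

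**Not stratifying is legitimate.** A reader might infer bias or an inflated error rate from leaving fear out of the lists. Randomisation rules out the first, and step 5 shows no sign of the second. Nor do the documents rank fear above IQ or age as a predictor: they call the fear relationship strong and the IQ research limited, which is not a ranking.

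**The gain is modest and can be negative.** This stands. If fear is weakly or not predictive, the adjusted test has about 2-4 points less nominal power, partly because the raw test runs at about 6% size. High fear may also be uncommon, since the children have no history of pain or treatment and the procedures are chosen not to hurt.

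**Conclusion.** The point holds as a cheap improvement, not as an error. A baseline score that the protocol collects, considers important and already adjusts for elsewhere is left out of the IQ-specific comparison that the trial is sized on. The cost is avoidable imprecision of about 1-9% in the SD of the IQ-specific risk difference (odds ratios 3-10, high-fear share 20-40%), plus unadjusted chance imbalance of 20 points or more in about 11-19% of IQ groups, or about 3% if only 10% of children have high fear. Every one of these sizes rests on an assumed fear share, and the precision figures also on an assumed fear effect. All rest on the within-IQ reading of the chi-squared test. It would go too far to conclude that the allocation scheme must change: once the analysis is adjusted, stratified lists add very little.

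**What to change.** In Statistical Analysis, state that arms are compared within each IQ group, and choose one of two fear-adjusted methods in advance:

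1. A Mantel-Haenszel test and risk difference within each IQ group, stratified by fear as faces 4-5 versus 1-3. This collapses the protocol's low and moderate levels, and the text should say so. The figures above apply to this option.
2. An IQ-by-arm term in the planned fear-adjusted logistic model, with the arm effect reported for each IQ group. This gives odds ratios rather than risk differences.

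The raw percentages can still be shown descriptively. The cost is a sentence or two of wording, with no extra children, visits or measurements, and the possible small power loss described above. The wording would also settle whether the comparison is within IQ group or pooled.

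Optionally, each IQ list could be split by the same fear category, giving six lists instead of three. The envelopes, now labelled with the child's name, would then have to be sequentially numbered, concealed and drawn after the FIS is scored. The added precision is slight (SD 0.126 to 0.124 in the middle setting), so this is a matter of preference.

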### **Outcome assessment**

The intervention will be video recorded, and the child's overall behavior in each test and control sub-group will be evaluated using FBRs at the end of the second

---

 bioseal ® Pit and Fissure Sealant, Biodinamica, Madrid. Spain

 Sorbet ® Fluoride gel, Keystone Industries, [name]. USA

visit by a blinded examiner (Appendix IV). Rating 1 (– –) will be given to the most negative child behavior and rating 4 (++) will be given to the most positive child behavior.

The face will be scored by giving a value of (1) to the most positive effect face and (5) to the most negative face. Faces with values (1,2) will indicate low dental fear, value (3) will indicate moderate dental fear, and faces with values (4,5) will indicate high dental fear. 

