# **Influence of active versus passive parental presence on the behavior of preschoolers with different intelligence and fear levels in the dental operatory: a randomized controlled clinical trial**

## **Abstract**

**Background:** Dental fear and anxiety still pose the most common factors proposed for the child's negative behavior in the dental operatory. Intelligence has an impact on the children's communication, feelings, and responsiveness to dental situations. The benefits of parental presence on reinforcing the child's behavior during dental treatment is still debatable. **Purpose of the Study:** The aim of this study is to assess the effect of parental active versus parental passive presence (PAP/PPP) technique on the overall behavior of preschool children with different intelligence and fear levels. **Methods:** This study will be two-parallel arms randomized controlled clinical trial. One hundred and fifty healthy children, 3-6-year-old, with no history of previous dental pain/treatment, and intelligence quotient (IQ) level of 70 -  $\leq 110$  will be recruited from the outpatient clinic of the Pediatric Dentistry Department, Faculty of Dentistry, Alexandria University, Egypt. In the first visit, the participants will be stratified into 3 equal groups (high, average, low) IQ using the Arabic version of Stanford Binet intelligence scale, fourth edition (SB- IV). In the second visit, dental fear will be assessed using facial image scale (FIS) followed by randomly dividing each IQ group into test and control sub-groups. During intervention, the control sub-groups will be managed using PPP technique, while the test sub-groups will be managed using PAP technique. The dental session will be video recorded and the overall behavior during treatment will be assessed using Frankl behavior rating scale (FBRs) at the end of the second visit.

**Clinical relevance:** This study aims to bridge the gap between the children's social/emotional development and their cognitive development, which has an impact on their behavior in the dental clinic. Moreover, it will also highlight the suitable parental role during treatment whether actively participating or only passively present with his child.

**Keywords:** Behavior modification, Dental fear, Intelligence quotient, Parental active/passive presence, Preschool children, Stanford Binet intelligence scale

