### **Calibration and reliability of examiner**

Prior to the study, the researcher will be calibrated by conducting training sessions with the supervisor for the application of the three measurement scales. Intra-examiner reliability will be assessed by the application of Facial Image Scale (FIS) and Frankl's Behavior Rating Scale (FBRS) to 10 children who will not participate in the study then they will be re-evaluated after 5 days. Then the results will be assessed using Kappa statistics.

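### The protocol claims a blinded examiner, but the arms differ in ways that an ordinary recording shows; no masking is described and the rater is not identified

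*Protocol*

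**What the plan says.** - **Outcome assessment.** "The intervention will be video recorded, and the child's overall behavior in each test and control sub-group will be evaluated using FBRs", at the end of the second "visit by a blinded examiner". The section does not say what the examiner is blind to (arm, IQ group, fear or hypothesis). The Abstract puts recording and rating side by side: "The dental session will be video recorded and the overall behavior during treatment will be assessed using Frankl behavior rating scale". Neither place says outright that the score is taken from the video.
- **Second visit.** In the test arm the parent is to "stand in close proximity to their child with hand holding and may help in explaining the dentist's instructions". In the control arm the parent sits behind the child without eye contact.
- **Calibration and reliability of examiner.** "the researcher will be calibrated by conducting training sessions with the supervisor for the application of the three measurement scales". Intra-examiner reliability is checked by applying the Facial Image Scale (FIS) and the FBRS "to 10 children who will not participate in the study then they will be re-evaluated after 5 days", summarised with kappa.
- **Statistical Analysis.** Behaviour is dichotomised into positive and negative. Test and control are compared by chi-squared test, and logistic regression models the dichotomised outcome.
- **Appendix IV.** The FBRS has four ratings, each defined by a short verbal description.

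**The concern.** The intervention is itself the position, touch and speech of the parent during the session that is recorded. Anyone who watches an unmasked recording, or sits in the room, would normally see or hear which arm the child is in. The protocol states that the rater is blinded but gives no step that would make it so.

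The outcome is open to this kind of influence. Adjacent FBRS ratings are separated by judgement: some negative attitude that is not pronounced, against acceptance with caution at times. The protocol does not state the cut, but it presumably falls between ratings 2 and 3. A rater who knows the arm and expects active presence to help could move borderline children across that cut in one arm only. The bias would enter the between-arm comparison directly, and the report would still describe the assessment as blinded.

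A second gap adds to the first. The only person calibrated is the researcher, and no section says whether the researcher is the blinded examiner. If it is someone else, the person who produces the outcome data has no planned calibration.

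**Working it through.** **1. Blinding claim against intervention.** No protocol figure is at issue, so this step sets the text side by side.

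| Element | What the protocol gives |
|---|---|
| Claim | Rating by a blinded examiner (Outcome assessment) |
| Material | The intervention session, video recorded (Outcome assessment, Abstract) |
| Test arm | Parent standing close, holding the hand, possibly speaking (Second visit) |
| Control arm | Parent seated behind, no eye contact (Second visit) |
| Masking of picture or sound | None described |
| What the examiner is blind to | Not stated |

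If the rating is live, both arms are plain. If it is made from an ordinary recording, hand holding and the parent's voice would normally mark the test arm, and their absence would mark the control arm.

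**2. Who rates.** The calibration section names the researcher; the outcome section names a blinded examiner. The calibration heading speaks of the examiner, which suggests one person, but no sentence joins the two. The plan supplies calibration of the rater only if they are the same person.

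**3. Size of the risk (illustration).** Inputs:
- 150 children allocated 1:1, so 75 per arm (Sample size estimation).
- Baseline probability of positive behaviour, p. The protocol gives 0.25 for low-IQ controls and 0.87 for healthy children. Halving the difference gives 0.25 + (0.87 − 0.25)/2 = 0.56. No rate is given for all controls together, so I take p = 0.25, 0.56 and 0.80 as assumptions.
- Share f of negative ratings upgraded to positive in the active arm only: 10% or 20%, both assumptions.
- No true effect.

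The apparent active-arm rate is q = p + (1 − p)f, so the spurious difference is (1 − p)f. The rejection rate sums the exact binomial probabilities of all 75 v 75 results for which the Pearson chi-squared statistic (no continuity correction) exceeds the two-sided 5% critical value.

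| p | f | q | Spurious difference | Rejection rate |
|---|---|---|---|---|
| 0.25 | 0 | 0.25 | 0 | 0.049 |
| 0.25 | 10% | 0.325 | 0.75 × 0.10 = 0.075 | 0.171 |
| 0.25 | 20% | 0.40 | 0.75 × 0.20 = 0.15 | 0.499 |
| 0.56 | 0 | 0.56 | 0 | 0.056 |
| 0.56 | 10% | 0.604 | 0.44 × 0.10 = 0.044 | 0.093 |
| 0.56 | 20% | 0.648 | 0.44 × 0.20 = 0.088 | 0.207 |
| 0.80 | 0 | 0.80 | 0 | 0.051 |
| 0.80 | 10% | 0.82 | 0.20 × 0.10 = 0.02 | 0.062 |
| 0.80 | 20% | 0.84 | 0.20 × 0.20 = 0.04 | 0.099 |

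If the comparison is made within one IQ group, 25 v 25, the rates at p = 0.25 are 0.095 and 0.215.

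**4. Reliability check.** As worded, the children are evaluated again after 5 days. For the FBRS, a second look at a child mixes real change in behaviour with inconsistency of the rater; scoring the same recording twice does not. The FIS is the child's own choice of face, so its repeat says little about the examiner. That is a minor side point, because the FIS is a covariate and not the outcome.

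**The case against.** The strongest reply is that masking may be intended and simply not written down. Camera framing is not given, a parent seated behind the child may be out of shot, and the examiner could be blind to IQ group, fear or hypothesis. This stands against one stronger reading. A reader might infer that the examiner cannot be blinded at all. The protocol does not support that, since tight framing could mask the arm at least in part. It does not rescue the plan as written, which asserts blinding and describes no method.

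A reader might also infer that the calibrated researcher is a different person from the examiner, so that the rater is certainly uncalibrated. No section says so, and the calibration heading points the other way. What stands is that the rater is not identified.

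A third inference is that a researcher who also applied the IQ test and the FIS would be unblinded by that. The protocol does not name who administers them. Knowing IQ or fear also does not reveal the arm: allocation is randomised within IQ groups, and fear is measured before allocation.

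Finally, 17% and 50% should not be read as the size of the problem. They apply the low-IQ control rate to every child. At higher baselines fewer ratings are negative and the effect shrinks, which is why a range is shown.

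**Conclusion.** The point holds in this form: the protocol claims blinded rating, its own intervention makes the arm visible and often audible in the rated session, and it provides no masking. Followed as written, the trial would normally produce a subjective, dichotomised outcome rated with the arm in view and reported as blinded. The rater's identity is also open, so calibration of the actual rater is not assured.

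Under the stated assumptions the false-positive rate at 75 per arm ranges from about 6% (p = 0.80, f = 10%) to about 50% (p = 0.25, f = 20%), against a nominal 5%. The upgrade shares and the common baseline are assumptions, not protocol values. The text cannot show whether any such upgrading would occur. The defect should be corrected before filming, because footage cannot be reframed afterwards.

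**What to change.** - Set one camera position for both arms, fixed on the child, with the parent and the held hand out of shot as far as possible.
- Have the FBRS scored from coded recordings by an examiner who is identified by role and did not attend the session. Adjust the text that times the rating at the end of the visit.
- Calibrate that examiner by scoring the same recordings of the 10 calibration children twice, 5 days apart, in place of re-examining the children. Do not present the FIS repeat as examiner reliability.
- State what the examiner is blind to. If voice or hand holding still reveals the arm, withdraw the claim of blinding to arm and say what blinding remains.

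Cost: changes of wording, a fixed camera position, and filming of the 10 calibration children. The camera, an examiner and those children are already planned. The drawback is that movement outside the frame is not scored, although the outcome is overall behaviour.
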